***Surgical complications***	
Postoperative ileus	Obstructive or paralytic symptoms after surgery with the need to suspend food intake and/or insert a gastric tube; this has to be confirmed radiologically (by abdominal sonography or plain abdominal X-ray or CT scan)
Postoperative hemorrhage	Need for administration of two or more red cell concentrates within the first 24 h postoperatively or need for reoperation
Surgical site infection	CDC definition [21]
Intra-abdominal abscess	Intra-abdominal collection of purulent or infected fluid (confirmed by culture) confirmed by puncture or by surgical reintervention
Anastomotic leakage	Grade A-C, Definition of grade according to International Study Group of Rectal Cancer 2010, diagnosed by CT scan with radiographic enema, endoscopy, drain secretion (stool) or reoperation
***Non-surgical complications***	
Thrombosis	Clinical evidence (for example, pain, swelling, warmth, erythema) of a leg or pelvic vein thrombosis confirmed by duplex sonography or CT angiography, which was not previously known
Pulmonary embolism	Clinical (for example, tachycardia, dyspnea) and/or radiological evidence of pulmonary embolism confirmed by spiral CT or lung perfusion scintigram
Postoperative pulmonary infection	At least three of the following:
	- temperature > 38°C
	- purulent tracheal secretion
	- leucocytes >12 or < 4.5 [10E9/L]
	- elevated CRP
	AND Evidence for pulmonary infection radiologically
Renal failure	Need for dialysis or hemofiltration
Cerebral insult	Ischemic or non-ischemic cerebrovascular event with persistent paresis or paralysis without previous history confirmed by CT or MRT
Myocardial infarction	Electrocardiogram (NSTEMI or STEMI) and enzyme (Troponin I) changes suggestive of myocardial infarction or needing admission to coronary care unit
*Serious adverse events*	SAE occurring from the day of randomization until regular end of trial follow-up or withdrawal
*Mortality*	All causes of mortality within 3 months after primary surgery
*Duration of surgical intervention*	First incision to the completion of skin closure (resection rectopexy) or the last coloanal suture (Delorme’s procedure)
*Length of initial hospital stay*	Means the hospitalization period from the primary operation date until the day of discharge (= postoperative hospital stay)
*Reoperation rate for recurrent prolapse*	Any surgical intervention for a recurrence
*Cumulative hospital stay*	Defined by the days in hospital after the primary surgery as well as the following hospitalizations due to complications or recurrence within 24 months after the primary operation
*Change of quality of life, constipation and incontinence*	
	Measured by means of the appropriate questionnaires SF-12, ( [22], validated in German), Herold constipation score ( [23], evaluated in German, but not yet published), Wexner-Score ( [10], non-validated in German, most commonly used score) and Rockwood-FIQLScore ( [24], validated), prior to the surgical intervention as well as 6, 12, and 24 months after the intervention

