### Scheme of intervention

DeloRes will be performed in 13 trial centers. All participating centers are cooperating units with a special focus on colorectal surgery and all centers perform between eight and sixty surgical interventions for rectal prolapse per year. In order to minimize performance bias, only surgeons with an adequate experience in performing the approaches investigated operate on patients in this study (minimum number of procedures performed (‘life-time experience’): Delorme’s procedure=20, (laparoscopic) resection rectopexy=20). Each study center provides at least one surgeon with the required experience for Delorme’s procedure and one surgeon with the required experience for (laparoscopic) resection rectopexy (expertise based, best team approach). To ensure standardization for all participating centers an operative manual with standardized video sequences will be prepared. Moreover, consented crucial steps of each procedure will be captured in the clinical record file. In addition, in order to allow confirmation of a certain procedure quality, selected digital photos will be taken.

To reflect current practice and to increase external validity of the trial, perioperative standards (for example, bowel preparation, parenteral nutrition, fast-track, postoperative application of laxatives) will not be strictly standardized. Each trial center, however, will document its own standards in a short questionnaire and agrees not to change this standard during trial recruitment.

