### Outcome measures and definitions

The clinically most relevant parameter in the treatment of full-thickness rectal prolapse is the time to recurrence. Therefore this parameter is defined as primary outcome measure, evaluated during the 24 months following primary surgery. Recurrence is defined as the circular protrusion of rectal mucosa through the anal canal and will be examined by standardized history, clinical examination, and photo documentation. To assess the primary outcome, patients are asked to perform a straining maneuver in a sitting position (patients not able to sit will be assessed in a lateral decubitus position). Then a photograph is taken during straining. The primary outcome is finally determined by the independent review board on the basis of the photograph.

Secondary endpoints are time to and incidence of recurrence of full-thickness rectal prolapse during 5-year follow-up, duration of surgical intervention, morbidity, SAE, all causes of mortality within 3 months after primary surgery (this period was chosen to get any mortality possible related to surgery. Patients with rectal prolapse are usually rather old and frail. There are multiple reasons for further morbidity or mortality which are expected to be unrelated to the surgical procedure in case they occur beyond the first 3 months), length of initial hospital stay, reoperation rate for recurrent prolapse, cumulative hospital stay and change in quality of life, constipation, and fecal incontinence as measured by appropriate questionnaires.

The time to and the incidence of recurrence of full-thickness rectal prolapse during a 5-year follow-up after primary surgery will be assessed as explained above. Morbidity occurring during the primary hospital stay is further differentiated into surgical and non-surgical complications, which are specifically defined as following: severity grading is done with the Clavien classification
[19] and for anastomotic leakage with the classification of the International Study Group of Rectal Cancer
[20]. The definitions of the secondary outcomes are shown in Table 
2. 

**Table 2 T2:** Definitions of secondary outcomes

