#### Analysis

The allocation of all patients to the different analysis populations will be defined prior to the analysis (full analysis set (FAS) according to the intention-to-treat principle (ITT; all randomized patients as randomized), per protocol (PP) analysis set, safety analysis set). The procedure of allocation will be documented in the statistical analysis plan. During the data review, deviations from the protocol will be assessed as ‘minor’ or ‘major’. Major deviations from the protocol will lead to the exclusion of a patient from the PP analysis set.

The confirmatory analysis is performed for the full analysis set. The null-hypothesis ‘no difference in the time to recurrence of full-thickness rectal prolapse between experimental and control intervention during the 2-year follow-up after randomization’ is tested by application of the log rank test stratified by center at the two-sided level α=5%. Drop-out and lost-to-follow-up without recurrence of full-thickness rectal prolapse are considered as censoring events.

For the analysis of the secondary outcomes descriptive methods will be used, including the calculation of appropriate summary methods for the empirical distribution as well as calculation of descriptive two-sided *P* values for comparisons of treatment groups. A special focus of the exploratory analyses will be on the time course of the primary as well as the secondary endpoints. Additionally, sensitivity analyses will be conducted for different study populations (per protocol population, appropriate subgroups). Further exploratory analyses will be performed to identify potential prognostic factors for the intervention effect. The time to recurrence of full-thickness rectal prolapse will additionally be analyzed applying a Cox regression model that includes covariates of potential prognostic value.

The safety analysis is based on all randomized patients who were treated with the interventions under investigation. The analysis includes calculation and comparison of the rates of specified complications (see secondary endpoints) and serious adverse events as well as of severity and relationship to intervention and graphical display of the time course. Furthermore, statistical methods are used to assess the quality of data and the homogeneity of intervention groups.

All analyses will be done using SAS version 9.1 or higher.

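### As worded, the myocardial infarction definition in Table 2 lets coronary care admission stand in for evidence of infarction, so events that are not infarctions can be counted as infarctions

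*Protocol article*

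**What the plan says.** The definition is in Table 2 (Definitions of secondary outcomes), under non-surgical complications: "Electrocardiogram (NSTEMI or STEMI) and enzyme (Troponin I) changes suggestive of myocardial infarction or needing admission to coronary care unit".

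It feeds the morbidity endpoint. Outcome measures and definitions states: "Morbidity occurring during the primary hospital stay is further differentiated into surgical and non-surgical complications". The same section assigns severity grading to the Clavien classification. It describes an independent review board, but only for the primary outcome, recurrence.

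The Analysis section uses these items to compare the arms: "The analysis includes calculation and comparison of the rates of specified complications (see secondary endpoints) and serious adverse events". It also fixes the status of the comparison: "For the analysis of the secondary outcomes descriptive methods will be used", with P values labelled descriptive.

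On local practice, Scheme of intervention says "DeloRes will be performed in 13 trial centers" and that perioperative standards "will not be strictly standardized". Each center documents its own standard and undertakes to keep it during recruitment. Treatment assignment and randomization specifies block randomization stratified by center.

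**The concern.** A complication definition should identify the complication it names. Here a level of care, admission to a coronary care unit, is offered as an alternative to findings that suggest infarction. Patients are admitted to such units for other reasons too, so the row can collect events that are not infarctions, and what it collects may depend on how a center uses its unit.

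Morbidity carries weight in how this trial will be read. The Discussion says that fewer recurrences after the abdominal procedure could be offset by higher morbidity. Complication labels therefore matter for interpretation even though no confirmatory test rests on them. Outcome measures and definitions describes the patients as typically old and frail, and ASA III patients are eligible, so cardiac events other than infarction are plausible.

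**Working it through.** There is no figure in the plan to reproduce. The check is of the wording, and of whether other text narrows it.

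**1. The possible readings.**
- *Plain reading:* (ECG and troponin changes suggestive of infarction) or (needing coronary care admission). Admission alone qualifies, whatever its cause. An arrhythmia without infarction would count. So would a pulmonary embolism managed in that unit, which also has its own row in the table.
- *Narrower reading:* ECG and troponin changes that are either (suggestive of infarction) or (such as to need coronary care admission). Both kinds of change must be present, but they need not suggest infarction if coronary care is needed. An arrhythmia without those changes does not count.

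The plain reading opens the row wide and the narrower one opens it only a little. Under both, something not suggestive of infarction can qualify.

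**2. Does other text close the gap?** No. The article gives no cardiac reason for the admission, attaches no diagnostic confirmation to that limb, and describes no adjudication of complications.

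**3. Comparison with the other rows of Table 2.** Thrombosis, pulmonary embolism, pulmonary infection and cerebral insult all call for imaging evidence. Renal failure and hemorrhage are defined partly or wholly by a need for treatment, but those treatments (dialysis or hemofiltration; transfusion or reoperation) bear directly on the named condition. Coronary care admission does not identify infarction in that way.

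**4. What it does to the comparison of arms.** Let p1 and p0 be the true infarction risks in the two arms, and f1 and f0 the chances that a patient without infarction is counted as having one. The expected recorded risk in an arm is p + (1 − p)f.
- If f1 = f0 = f, the recorded difference is (1 − f)(p1 − p0). With no true difference it is zero. With a true difference it shrinks slightly, and the ratio of the two risks moves toward 1.
- If p1 = p0 = p but f1 ≠ f0, the recorded difference is (1 − p)(f1 − f0), a spurious effect.

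Stratifying randomization by center puts each center's admission practice on both arms about equally, which is the first case. The second case needs coronary care use to differ by procedure within centers.

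**5. Size.** Sizing needs p and f. The article gives neither an infarction rate nor a coronary care admission rate, so no number follows from it.

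**The case against.** The strongest reply is that this is loose wording with little consequence. The row is headed myocardial infarction, and the ECG criterion carries a parenthesis naming two infarction types, so investigators would probably apply it to infarctions. Need-based criteria appear elsewhere in the table. The item is one of eleven listed complications in a secondary endpoint analysed descriptively. Most of this stands, and it limits the point to a minor one. It does not remove it: the heading and the parenthesis suggest an intention, while the wording still supplies an alternative route into the count.

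Three stronger readings are tempting, and the article does not support them.

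- *A reader might infer that non-infarct events are in fact being counted.* The article reports no events. It shows only that they can be.
- *A reader might infer that local bed policy distorts the comparison of arms.* Coronary care admission is not among the examples of non-standardized practice, centers undertake to keep their standards constant, and stratified randomization spreads center differences over both arms. A difference by procedure is conceivable, since the article calls perineal repair less invasive, shorter and possible under spinal or epidural anesthesia. But nothing says that either operation leads to different coronary care use, and the definition speaks of need, not of routine monitoring.
- *A reader might want to state the share of false infarctions.* That share only returns what is put in. Assuming, from outside the article, infarction in 1% to 2% and non-infarct coronary care admission in 1% to 5%, it runs from 0.01/(0.02 + 0.01) = 33% to 0.05/(0.01 + 0.05) = 83%. The range applies only on the plain reading and says nothing about a difference between arms.

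Double counting of a pulmonary embolism likewise needs the plain reading, and the article defines no summed event count in which it would matter.

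**Conclusion.** The point holds as a minor defect of definition. Coronary care admission is written as an alternative to evidence of infarction, and nothing else in the article narrows it, so events that are not infarctions can be counted as infarctions: any such admission on the plain reading, or ECG and troponin changes not suggestive of infarction on the narrower one.

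The size cannot be derived from the article. The expected effect is misclassification noise in one component of secondary morbidity. Bias between arms would follow only if coronary care use differed by procedure within centers, which the article neither states nor excludes. The confirmatory log rank test on recurrence is untouched.

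**What to change.** In Table 2 and the CRF, require ECG and troponin changes suggestive of infarction for every event counted as myocardial infarction, and delete coronary care admission as an alternative criterion. Record coronary care admission as a separate item. Severity needs no new instrument, because Clavien grading is already planned. This concerns only how events are classified and changes no patient's care.

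Because recruitment was under way (34 of the planned 130 patients randomized by June 2012, according to Trial status), cardiac events already recorded should be re-checked against the revised definition so that one rule applies to all patients.

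The cost is one line in the table and the CRF, a brief review of existing paper CRFs, and a smaller cardiac count. Admissions that leave the infarction row remain visible in the separate item.

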### Data management

All protocol-required information collected during the trial must be documented in the paper-based CRF by the investigator. Any outstanding entries must be completed immediately after the final examination. The completed CRF must be reviewed and signed by the investigator named in the trial protocol.

In order to ensure that the database reproduces the CRFs correctly a double entry of data will be performed by two different people.

### Compliance/rate of loss to follow-up

To reduce the number of patients not able or willing to visit the study centers a study nurse will be appointed to visit the patients and to assess the outcome at the specified time (‘flying study-nurse’). Furthermore, the time-to-event method will be applied for the primary analysis to allow for all available information including the observation time of patients who drop out early. Nevertheless, an additional percentage of patients will be recruited to assure a sufficient power for the confirmatory analysis.

### Safety assessments and reporting of adverse events

Analysis of safety-related data is performed with respect to frequency of serious adverse events, frequency of serious adverse events stratified by intensity and causality, and frequency of morbidity in both treatment groups.

From the day of randomization until the regular end of trial follow-up or until premature withdrawal of the patient, all serious adverse events must be documented on a ‘serious adverse event form’ available in the investigator site file.

A serious adverse event will be defined as an event that results in death, is immediately life-threatening, requires or prolongs hospitalization beyond the 20th postoperative day for any medical reason, requires readmission for any medical reason within 3 months after the operation within this trial, requires readmission for treatment of surgical complications related to the study operation beyond 3 months postoperatively, or results in persistent or significant disability or incapacity. Serious adverse events will be classified in intensity (mild, moderate, severe), outcome (recovered completely, recovered with sequelae, not recovered, death, unknown), and causality (unrelated, possibly related, probably related, definitely related, not assessable).

The assessment is based on surgical findings and the clinical course of the patient. It needs to be done by the investigators. Serious adverse events have to be reported by the attending physician to the coordinating investigator or one of both study supervisors within 24 h after the SAE becomes known.

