### Data and safety monitoring board (DSMB)

To enable an independent risk assessment for the different surgical procedures, potentially related serious adverse events will be noted and periodically assessed by the independent Data and Safety Monitoring Board (DSMB). Detailed working procedures are defined in a different document.

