[32] compared abdominal to perineal surgical approaches for rectal prolapse in a pragmatic two-stage randomization trial design depending on the surgeons degree of uncertainty which of four approaches to choose. The study was able to recruit 293 patients from 33 centers over a 7-year period from February 2001 up to the cessation of the trial in August 2008, but only 26 patients were actually randomized to one of the two approaches (last available newsletter from December 2005, see trial website). All other patients were allocated to one of the two procedures by surgeon’s preference. In view of the very small number of patients actually randomized to a perineal versus an abdominal approach, the conclusions of this study are going to be very limited and the risk of selection bias is high. In addition, the majority of recruiting centers recruited less than 10 patients to the study, further reducing the validity of the results.

Considering the lessons learned from the PROSPER Trial, an urgent need currently exists for an adequately powered, simple parallel-group randomized trial comparing the abdominal to the perineal approach in rectal prolapse. Contrarily to the PROSPER Trial, clinical equipoise regarding the two surgical approaches has been concluded after extensive discussion of the available data as the confidence intervals of the published studies on the two approaches overlap considerably. Even if the study shows that the abdominal procedure results in significantly less recurrences this may be outweighed by a considerably higher morbidity and possibly less improved quality of life. This trial therefore only allows randomization to a perineal or abdominal approach. A loss of eligible patients to an observational non-randomized arm, as was the case for the majority of patients in the PROSPER Trial, will not be possible.

This trial is designed as an expertise-based trial aiming at strong internal validity by high performance and standardization. Generalizability may be reduced by the expertise-based trial design. However, this type of surgery in larger numbers is predominantly performed by specialized surgeons. For these surgeons but also for general surgeons operating only on a few cases per year the results of this trial should have an important impact on clinical practice by determining the most effective treatment for rectal prolapse.

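### Whether a re-operated index-stay complication counts as an SAE depends on discharge date, so the SAE comparison between arms and expedited reporting depend partly on length of stay

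*Protocol article*

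**What the plan says.** The section on safety assessments and reporting of adverse events counts an event as an SAE if it "requires or prolongs hospitalization beyond the 20th postoperative day for any medical reason, requires readmission for any medical reason within 3 months" of surgery. The other routes to SAE status are death, an immediate threat to life, lasting disability and, once 3 months have passed, a readmission to treat a surgical complication of the study operation.

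The list names neither re-intervention nor a stay that was prolonged but ended by day 20. SAEs go on a dedicated form and are reported within 24 h. The steering committee must be told of them promptly. The section on the DSMB gives that board this task: "To enable an independent risk assessment for the different surgical procedures, potentially related serious adverse events will be noted and periodically assessed".

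Morbidity is a separate secondary endpoint. For complications of the primary stay, "severity grading is done with the Clavien classification", with a further classification for anastomotic leakage. Table 2 defines leakage, haemorrhage (including haemorrhage needing reoperation) and intra-abdominal abscess. The safety analysis compares both the specified complications and the SAEs between arms, and SAEs are also a named secondary outcome.

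**The concern.** The two hospital-based criteria use different thresholds. Before discharge, an event counts through hospitalization only if the stay runs past day 20. After discharge, any readmission in the first 3 months counts, however minor its cause. Seriousness then depends partly on whether the patient had gone home when the event occurred.

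This matters for two reasons. First, the trial has to weigh fewer recurrences against the burden of abdominal surgery; the Discussion says of a recurrence benefit that "this may be outweighed by a considerably higher morbidity and possibly less improved quality of life". SAE frequency is one of the planned safety comparisons, and if the arms differ in discharge timing, the rule alone can create or hide a difference. Second, some re-operated index-stay complications bypass the expedited route that alerts the oversight bodies during the trial.

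**Working it through.** The plan states no figure to reproduce. The check applies the definition to cases, traces the consequences, and then shows by illustration how the count behaves.

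**Step 1: one event, two discharge dates.** Take an anastomotic leak or bleed re-operated on day 8, judged not immediately life-threatening and leaving no lasting disability. Patient A went home on day 5 and is readmitted, leaving again before day 20. Patient B is still an inpatient and goes home on day 19.

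| Criterion | A | B |
|---|---|---|
| Death or immediate threat to life | no | no |
| Hospitalization past day 20 | no | no |
| Readmission within 3 months, any reason | yes | no |
| Later readmission for a related surgical complication | no | no |
| Lasting disability | no | no |
| **SAE** | **yes** | **no** |

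A readmission in month 2 for a minor, unrelated reason is also an SAE. The day-20 clause could be read so that any event requiring hospitalization qualifies, but the separate readmission criteria would then be redundant. The reading in the table is the natural one. It is the hospitalization, not the complication, that must pass day 20.

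**Step 2: what B's event still enters, and what it misses.** It enters the morbidity endpoint with a Clavien grade and is compared by arm in the safety analysis. It misses the SAE form, the 24 h report, the steering committee notice and the DSMB's assessment of potentially related SAEs. The stopping guidelines also promise the DSMB relevant safety data at regular intervals, but do not say whether such events are included.

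**Step 3: can discharge timing differ by arm?** Length of initial stay is itself a secondary outcome. The Discussion calls perineal approaches less invasive, and the scheme of intervention leaves fast-track care to each center. Center-stratified randomization balances center habits but not a difference caused by the procedure. No length of stay by arm is given.

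**Step 4: illustration with assumed inputs.** Let p be the true rate of complications needing re-intervention (equal in both arms), q the share occurring after discharge, and r the share of in-hospital ones that count anyway (past day 20, life-threatening, fatal or disabling).

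Counted SAE rate = p × (q + (1 − q) × r)

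Assume p = 10%, r = 20% and abdominal q = 0.2:

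- Abdominal: 10% × (0.2 + 0.8 × 0.2) = 3.6%.
- Delorme, q = 0.5: 10% × (0.5 + 0.5 × 0.2) = 6.0%; ratio 6.0/3.6 = 1.67.
- Delorme, q = 0.3: 4.4%; ratio 1.22.
- Delorme, q = 0.7: 7.6%; ratio 2.11.

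With 65 patients per arm, the central case is 65 × 6.0% = 3.9 against 65 × 3.6% = 2.3 counted events. The share not counted is 1 − 6.0/10 = 40% (Delorme) and 1 − 3.6/10 = 64% (abdominal).

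The result depends heavily on r. With q = 0.5 against 0.2:

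| r | Delorme | Abdominal | Ratio | Not counted |
|---|---|---|---|---|
| 20% | 6.0% | 3.6% | 1.67 | 40% / 64% |
| 50% | 7.5% | 6.0% | 1.25 | 25% / 40% |
| 80% | 9.0% | 8.4% | 1.07 | 10% / 16% |

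The ratio does not depend on p. With equal q it is 1, and if the abdominal arm had the larger q the distortion would run the other way.

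**The case against.** The strongest reply is that the plan has two channels: graded morbidity for the primary stay and readmission criteria for what follows. Patients A and B are both recorded, one as an SAE and the other as morbidity. The trade-off in the Discussion is framed in terms of morbidity, the day-20 clause does not touch the morbidity data, and the SAE comparison is descriptive only.

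Much of this stands, and it rules out some stronger readings:

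- A reader might infer that re-operated leaks and bleeds go unreported. They do not; they are defined, graded and compared by arm. What they escape is SAE classification and what follows from it.
- A reader might infer that the DSMB never sees them. The article does not show that: the board also receives safety data of unspecified content, and its working procedures are in a separate document not at hand.
- A reader might infer that the threshold removes most serious in-hospital complications. That would only restate an assumed small r; the documents give no value, and some re-operated events will be judged immediately life-threatening.

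Two things are left unanswered. SAE frequency is a planned between-arm comparison in its own right, and printing morbidity beside it does not make it independent of discharge date. The article also ties differentiated, graded morbidity to the primary stay, so an event that falls after discharge can move from one count to the other. Neither count alone is then sure to cover all events of a given severity.

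**Conclusion.** The point holds as a defect in the definition. Some re-operated index-stay complications fall outside SAE status, and so outside expedited reporting and SAE-based oversight, solely because the patient had not yet been discharged and left by day 20. The between-arm SAE comparison depends to that extent on discharge timing.

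The textual reading needs no assumption beyond the event being judged neither immediately life-threatening nor disabling. The size of any bias cannot be estimated from the documents. The ratios of 1.07 to 2.11 show only that the rule can produce an apparent difference when true risks are equal. They rest on assumed q and r, and vanish if discharge timing is the same in both arms. It would go too far to conclude that the SAE comparison will be biased against Delorme's procedure by a stated amount. The primary analysis of recurrence is not affected.

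**What to change.** Reconcile the SAE definition with the morbidity definitions:

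1. Add to the SAE definition that an event requiring surgical, endoscopic or radiological re-intervention, or intensive care (Clavien grade III or higher), is an SAE on any postoperative day.
2. Reclassify patients already treated from their recorded Clavien grades. The article reports 34 of the planned 130 randomized by June 2012, so an amendment at that point would have covered the other 96 prospectively.
3. Present the SAE comparison alongside Clavien III or higher events counted irrespective of discharge date. The article states Clavien grading for the primary stay; if later complications are not graded, their readmission records would need the same grade.

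The cost is a wording amendment, some additional SAE forms and possibly the grading of readmissions. Two limits remain. Any-cause readmission within 3 months would still make minor events discharge-dependent. A criterion based on prolongation of the initial stay is not a good substitute, because the article gives no reference stay and perioperative standards vary by center.
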